# Using implementation mapping to optimize the impact of Universal School meals: a type III hybrid implementation-effectiveness study protocol

**DOI:** 10.1186/s43058-025-00769-y

**Published:** 2025-10-01

**Keywords:** Universal school meals, Food insecurity, Obesity policy, Equity, Implementation mapping, Implementation strategies, Community-engaged research

## Abstract

**Background:**

Provision of government subsidized school meals at no charge to all students in income-eligible schools (Universal School Meals) is a critical policy approach to address food insecurity and risk for obesity in school-aged children. However, despite documented benefits, implementation challenges remain, which limit the uptake and associated impact of this provision. To ensure the longevity of this policy approach, equity-focused solutions that center the needs of those tasked with implementation and the most vulnerable Universal School Meals recipients are necessary. The aims of this study are to develop equity-focused implementation strategies and test them through a hybrid type III cluster-randomized trial to examine potential effectiveness on improving student uptake and implementation across the school system.

**Methods:**

Aim 1 will comprise the first tasks of Implementation Mapping to co-develop implementation strategies in partnership with school implementers and recipients to ensure contextual fit within their school system. Aim 2 will comprise the final step of implementation mapping with a hybrid type III implementation-effectiveness trial to examine primary implementation and effectiveness outcomes of the applied strategies. Reach and penetration will be the primary implementation outcomes in addition to acceptability, feasibility, cost, and sustainability. Health outcomes comprise family food security, student dietary behaviors, and body mass index. Baseline, 6-month, and 12-month assessments will be recorded. A convergent (Quantitative–Qualitative) mixed methods design will be employed for analysis; exploratory hierarchical multiple regression models will be run for each behavioral outcome using students as the unit of observation and schools as the unit of analysis. Survey and interview data for implementation outcomes will be analyzed deductively according to the Exploration, Preparation, Implementation, and Sustainment and Getting to Equity frameworks then inductively to generate overarching themes across the trial period.

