This pilot intervention will utilize an evidence-based process (i.e., implementation mapping) [38] and test primary implementation outcomes of penetration and cost, [48, 49] and secondary impact on student health outcomes (i.e., weight status, food security, dietary behaviors).

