The GTE [7] and the Exploration, Preparation, Implementation, Sustainment (EPIS) [53] frameworks will ground Aim 1 (Tasks 2–4) to guide the selection and tailoring of implementation strategies and protocols [7, 54]. The GTE was developed to inform operationalization of equity principles and concepts in PSE approaches related to obesity, in partnership with members of the community of interest. GTE guidance prompts for identifying and addressing intervention design features and contextual variables to improve equity impact, accounting for individual and community-level resources and capacity [7]. The EPIS framework [53] conceptualizes key phases of Exploration (deliberating ways to innovate/the innovation), Preparation (planning for implementation), Implementation (the process of implementing), and Sustainment (maintaining implementation) that guide and describe the implementation process. Similar to CFIR, EPIS provides a set of constructs among key domains of outer context (outside the school system) and inner (within school) context across these phases, bridging factors that span across inner and outset settings, innovation factors, and role of innovation adopters. Together, these frameworks will support the co-development process, ensuring that strategies and protocols developed are grounded in addressing inequities in access (GTE), and that we have a strong structure (EPIS) that facilitates consideration of key determinants and processes over discrete phases of the mapping process.

Primary implementation outcomes aligning with Proctor et al.’s framework [55] will be collected in Aim 2 (Task 5) to evaluate the resultant implementation strategy through a Hybrid Type III Design [56]. Chosen outcomes are penetration (i.e., degree to which school meals were provided equitably to low-income students) and cost (i.e., time, labor, supplies needed). Additional implementation outcomes include acceptability (i.e., degree of satisfaction); feasibility (i.e., practicality of strategy); and sustainability (i.e., maintenance of intervention) [57]. Secondary student-level outcomes will be assessed to understand behavioral impact of the implementation strategy on student weight status, family food security, and dietary behaviors. The EPIS framework will also support evaluation of key implementation determinants and processes over the evaluation period to triangulate implementation and behavioral outcome data.

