### Aim 2: evaluate implementation and student-level outcomes of the strategy using a hybrid type III implementation-effectiveness design

Following the hybrid type III approach, [56] a longitudinal convergent (Quantitative–Qualitative) mixed-methods design will investigate the impact of this trial. Primary implementation outcomes of penetration/reach will be calculated through analyzing participation rates from breakfast and lunch service across the implementation period. We will create an implementation costing measure to calculate the financial cost of each implementation strategy. Additional outcomes of acceptability (i.e., are representatives satisfied with this strategy?), feasibility (i.e., was this simple to carry out?), and sustainability (i.e., could this be maintained?) will be assessed from the perspective of implementers. Implementation objectives identified in Task 2 will be evaluated through brief, semi-structured interviews with implementing representatives*.* Secondary student health outcomes of weight status, food insecurity, and dietary behaviors will be analyzed over the 2-year implementation period.

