#### Analyses

Overall, the longitudinal data collection at baseline, 6 months, and 12 months following the inception of the trial will facilitate assessment of change over time and identification of factors that influence the outcomes. For the implementation outcomes, penetration will be analyzed by calculating the proportional change in number of low-income students participating in USM from prior to enacting the implementation strategy at baseline, 6 months, and 12 months following the start of the trial. For the costing measure, labor costs will be iteratively analyzed through the bottom-up approach to collect time and effort data from all implementing individuals; salary data will be obtained for all SDP positions through review of publicly available records. Receipts and invoices for all materials and miscellaneous costs will be analyzed. All costs will be calculated specific to each strategy to allow for accurate reporting and budget impact assessment showing net financial costs resulting from the strategies. The costconsequence analysis will be conducted to show the comparison of the costs and outcomes of each strategy in comparison to the waitlist condition (i.e., treatment as usual) [49, 72]. Data from the acceptability, feasibility, and sustainability surveys will be processed and aggregated at the school level to provide overall means. Interview data on other outcomes identified through the mapping procedure will be analyzed deductively through the GTE and Proctor outcomes framework [7, 57] followed by mapping ongoing determinants to the EPIS framework in the Implementation and Sustainment phases, providing tangible barriers and facilitators across the trial period [53]. This will enhance continuation of determinants analysis from Aim 1 and support adaptation/tailoring of the implementation strategies over time in response to needs/challenges at each school. Such adaptation is recommended by implementation science experts as a means to enhance equity through collaborations with community and clinical partners [43].

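### The primary implementation outcomes are worded three ways, and penetration, the only constant among them, has no single definition and no stated contrast with the waitlist

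*Protocol article*

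**What the plan says.** Five places in the protocol article assign primary status.

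- Abstract, Methods: "Reach and penetration will be the primary implementation outcomes in addition to acceptability, feasibility, cost, and sustainability".
- Background, closing paragraph: the study will "test primary implementation outcomes of penetration and cost". The Summary repeats this.
- Theoretical framework and preliminary findings: under the label of primary implementation outcomes, "Chosen outcomes are penetration (i.e., degree to which school meals were provided equitably to low-income students) and cost (i.e., time, labor, supplies needed". It continues: "Additional implementation outcomes include acceptability (i.e., degree of satisfaction); feasibility (i.e., practicality of strategy); and sustainability (i.e., maintenance of intervention". Cost is not in that second list.
- Aim 2, opening paragraph: "Primary implementation outcomes of penetration/reach will be calculated through analyzing participation rates from breakfast and lunch service across the implementation period". The next sentence is "We will create an implementation costing measure to calculate the financial cost of each implementation strategy", with no label. Acceptability, feasibility and sustainability then follow as additional outcomes.

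Two further places say how penetration is measured. Table 1 has a single row for it, glossed as meal participation and summarised as a monthly percentage for each student. The Aim 2 Analyses section says that "penetration will be analyzed by calculating the proportional change in number of low-income students participating in USM", at baseline, 6 months and 12 months.

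**The concern.** A reader of the final report should be able to tell from the protocol which result was primary. Here the answer depends on which section is read. Cost is primary in three places, grouped with the other outcomes in one and unlabelled in one. Reach is a separate outcome in one place, joined to penetration in another and absent from the primary set in three.

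The agreement on penetration does not settle the matter, because the word covers different quantities. They differ in population (all students or low-income students), metric (rate, per-student percentage or head count), meal, and time (the whole period, monthly, or 6 and 12 months). The analysis sentence for penetration describes a change from baseline and does not set it against the waitlist schools, although that comparison is the reason for randomising.

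At stake is whether the pilot's main finding on participation can be read as a randomised comparison of a measure fixed in advance, and whether the later, larger trial that it is meant to inform inherits a clear outcome.

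**Working it through.** The document gives no figure to reproduce: it states no alpha, power, effect size or success threshold for any primary outcome. The check is a comparison of the text, with a short piece of arithmetic on the metric.

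**Step 1. The primary set.**

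| Place | Labelled primary | Cost | Reach |
|---|---|---|---|
| Abstract, Methods | reach, penetration | grouped with acceptability, feasibility, sustainability | named separately |
| Background, end | penetration, cost | primary | not named |
| Theoretical framework | penetration, cost | primary | not named |
| Aim 2, opening | penetration/reach | unlabelled | joined to penetration |
| Summary | penetration, cost | primary | not named |

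**Step 2. Can the Abstract be reconciled with the rest?** Its *in addition to* can be read two ways.

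- Two primaries and four other outcomes: cost is then not primary, against the Background, the framework section and the Summary.
- Six primaries: acceptability, feasibility and sustainability are then primary, against the framework section, which calls them additional.

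Either reading leaves a conflict. The Aim 2 opening does not contradict the three agreeing places outright, since it leaves cost unlabelled.

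**Step 3. The forms of penetration.**

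| Place | Form | Population | Time |
|---|---|---|---|
| Theoretical framework | equity of provision | low-income students | none given |
| Aim 2, opening | breakfast and lunch participation rates | not restricted | whole implementation period |
| Table 1 | percentage per student | not restricted | monthly |
| Aim 2, Analyses | proportional change in number participating | low-income students | baseline, 6 and 12 months |

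**Step 4. Why the form matters.** Let E be the number of low-income students enrolled and r their participation rate, so the number participating is N = E × r. Then

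proportional change in number = (E1/E0) × (r1/r0) − 1.

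If the rate does not move (r1 = r0), this equals E1/E0 − 1, so the number follows enrolment alone.

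Relative and absolute change also differ by meal. The Background gives participation of 30–40% for breakfast and 50–60% for lunch. Taking the ends of those ranges purely as an illustration of a 10-point move:

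- breakfast: (40 − 30)/30 = 33.3% proportional change;
- lunch: (60 − 50)/50 = 20.0% proportional change.

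The same 10-point gain looks larger for breakfast on the proportional scale. These are not predicted effects.

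**Step 5. The contrast.** Participants and procedures says that penetration data will be collected in all four schools, so a between-arm comparison is possible. In the Analyses section, the intervention-versus-control models are specified for the behavioural outcomes. The only implementation analysis there that mentions the waitlist is the cost-consequence analysis.

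**The case against.** Much can be said on the other side. Three of the five places agree word for word or in substance, and the Aim 2 opening has the same list of additional outcomes as the framework section. The outlier is one ambiguous sentence in an abstract. No separate reach measure is planned, since Table 1 has one row. The cost-consequence analysis does set the outcomes of each strategy beside the waitlist. All of this stands. It makes the conflict narrower and easy to repair, but it does not supply a definition of penetration or name the contrast for it.

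Three stronger readings are tempting, and the documents do not support them.

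- *The primary outcome can be picked after the data are seen.* Penetration is primary in every version and cannot be swapped out. The trial is registered, and neither the registry record nor any analysis plan is at hand; either may fix the set.
- *The false-positive rate is inflated.* One might count breakfast and lunch at 6 and 12 months as four tests at 5% and compute 1 − 0.95^4 = 18.5%. No such tests are planned, no alpha is stated, and independence is implausible because the results come from the same schools and largely the same students. With four schools in two pairs there are 2 × 2 = 4 allocations, so the smallest school-level randomisation p-value is 1/4 = 0.25 one-sided or 2/4 = 0.50 two-sided. Four 5% tests do not describe this design.
- *Cost cannot be primary because usual-practice schools have no strategy to cost.* A hybrid type III study may have a descriptive primary implementation outcome, and the protocol claims no randomised effect on cost. What is missing is one clear statement of its status.

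**Conclusion.** The inconsistency is real and is worth correcting. The firm conflict is between the Abstract on one side and the Background, framework section and Summary on the other; the Aim 2 opening adds an ambiguity about cost. Separately, penetration has four forms in four places. The one attached to the analysis is a change in number that mixes enrolment with uptake and has no stated comparison with the waitlist.

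The consequence is a risk of selective emphasis: between participation and cost, between meals, and between time points and metrics. This cannot be expressed as an error rate, and in a four-school pilot with no success rule it does not undermine a confirmatory claim, because none is made. The conclusion rests on the published article alone. A registry entry or analysis plan might fix one set, but any single set would still disagree with at least one place in the article.

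**What to change.** Use one statement of the primary implementation outcomes in the Abstract, the Background, the theoretical framework section, the opening of Aim 2 and the Summary. Carry the same definition into Table 1 and the Aim 2 Analyses, and check that the registration agrees.

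- Say that reach and penetration are one measure.
- Define it as the participation rate of low-income students, with that group's enrolment as the denominator. Compare it as (change from baseline in intervention schools) − (change from baseline in waitlist schools).
- Name one time point. Twelve months would match the behavioural outcomes; the authors should confirm that the waitlist schools are still on usual practice then. The 6-month and monthly figures become supporting results.
- Report breakfast and lunch as two named components, always together.
- State cost's status once: either a descriptive co-primary implementation outcome with no randomised test, as the Background, framework section and Summary imply, or a secondary outcome.

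The cost is wording and a registry check. No data are lost, and every outcome is still collected and reported. If the authors choose the second option for cost, it loses only the primary label.

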**Discussion:**

This implementation mapping process will yield equity-driven strategies, which can be successfully implemented in school settings to improve uptake of USM and reduce food insecurity and obesity-related disparities in high-risk youth. This study presents a rigorous and equity-driven implementation research agenda with the potential to advance school-based obesity prevention efforts by identifying, developing, and evaluating context-specific strategies that meet the needs of vulnerable student populations.

**Trial registration:**

ClinicalTrials.gov, NCT06579079, Registered on 11–5-2024.

**Supplementary Information:**

The online version contains supplementary material available at 10.1186/s43058-025-00769-y.

Contributions to the literature
This study marks a much-needed alignment of implementation science and health equity to address disparities in food insecurity and obesity risk through community-engaged implementation mapping methodologyPartnerships created with a local school district facilitate the use of natural experiment research so that we can study the impact of the Universal School Meals implementation strategy in real-time and commence efforts to scale up strategies to be applied across the district starting immediately after the trial.This study uniquely contributes to the literature by examining Universal School Meals implementation in an urban city with large racial and ethnic minority populations, providing urgently needed evidence on how to tailor and sustain school-based nutrition interventions in historically marginalized communities most affected by structural inequities in food access and health outcomes.

## Background

Children living in low-income situations are more than twice as likely to experience food insecurity than more affluent counterparts [1–3]. Risk for food insecurity is heavily linked to risk for obesity; [4] this relationship is heightened in populations with low income. Given the complex, community and population-level factors that influence health outcomes (i.e., poverty, discrimination, inadequate access to healthy food) [5], policy, systems, and environmental (PSE) approaches are necessary to mitigate obesity risk and achieve equitable outcomes for socially and economically marginalized populations such as and racial/ethnic minorities and those with low-income [6–8]. School-based PSE interventions, such as those which promote healthy eating and physical activity through enhancing the school environment, show promise for preventing obesity [9–12]. However, this impact remains limited because most interventions have not been designed with consideration of long-term implementation and sustainability [13, 14].

For the last six decades in the US, the National School Lunch Program [15] and the National Breakfast Program [16] (NSLBP) have been combatting food insecurity among children with low-income backgrounds. These programs are the primary federal food safety net for school-aged children. Universal School Meals (USM) operate through a policy called Community Eligibility Provision, which allows all schools and districts serving more than 25% low-income students to provide free breakfast and lunch under the NSLBP [17]. Several states have now moved to state-wide USM to address growing rates of food insecurity [18]. Research has shown that providing healthy school meals to students via USM is associated with higher quality nutritional intake and reduced obesity prevalence, especially in low-income students [8, 19–21]. Thus, increasing access to healthy meals at school is a critical step to mitigating disparities in obesity prevalence in youth [20]. USM adoption is also positively associated with quality of dietary intake, food security, and academic achievement outcomes observed through randomized trials and longitudinal studies [22–24]. Therefore, USM is a key PSE approach for equitable obesity prevention.

Despite the many benefits associated with USM, schools cite logistical challenges (i.e., lack of staffing for implementation, limited space) and lack of uptake among students [25]. Reports highlight consistent increases in adoption among eligible schools and districts over the last 10 years, [17] yet student participation in USM remains low; available data indicate only 30–40% of students partake in breakfast and 50–60% in lunch [26]. These trends are reflected in the School District of Philadelphia (SDP) [27, 28]. Programs and policies designed to mitigate health disparities for food insecurity and obesity cannot make the most impact if they are not reaching their target population. Because the federal reimbursement rate for schools is tied directly to participation (i.e., the more meals taken, the more reimbursement the district receives), maintaining reach is critical to making USM financially feasible. Students who do not participate in school meals are more likely to purchase unhealthy foods from outside retailers (e.g., corner stores), [29, 30] increasing risk for overweight and obesity [31]. Negative impacts on school climate, [32] school finances, [24] and household food insecurity [24, 33] highlight the need for efforts to increase reach among low-income youth, especially adolescents where prevalence of food insecurity and obesity are highest [34]. Thus, optimizing reach of USM will enhance its impact on addressing disparities in child obesity.

Dissemination and implementation science facilitates the process by which evidence-based interventions (EBIs) are implemented and sustained in practice [35, 36]. Through this lens, the desired outcome is implementation effectiveness as a means to reach clinical effectiveness (i.e., obesity prevention). This is achieved by developing implementation strategies, which are designed to enhance implementation of EBIs [37]. Such strategies can be chosen through a variety of ways, but implementation mapping is a key method to ensure a community-driven process [38]. Implementation mapping is based on intervention mapping and instead of developing new interventions, focuses on co-creation of implementation strategies through accomplishing five key tasks: 1) Needs Assessment; 2) Identify Outcomes; 3) Select Implementation Strategies; 4) Develop Implementation Protocols; and 5) Evaluate Outcomes. Although implementation science provides systematic approaches for increasing real-world impact of obesity prevention, health equity is not explicitly considered [39]. Recent advancements have introduced health equity as a key focus [40–43], including the Consolidated Framework for Implementation Research (CFIR version 2) [44, 45] and the Getting to Equity (GTE) [7] framework for obesity prevention, which stresses that reducing disparities requires community-engaged strategies that 1) provide healthy options (e.g., healthy school meals), 2) reduce barriers (e.g., stigma), 3) improve individual social and economic resources, and 4) build on community assets and capacity [7]. Accordingly, leveraging implementation strategies to improve USM implementation is critical for equitable access to USM [46].

Given our previously conducted needs assessment [47], this study will accomplish the development and testing of an equity-focused implementation strategy for USM to promote improved uptake of healthy school meals among school students in Philadelphia, United States. Specifically, the aims of this study are to:Aim 1: Use a community-engaged procedure to develop an equity-focused implementation strategy through a cluster randomized trial.Aim 2: Evaluate implementation and student-level outcomes of the equity-focused strategy using a hybrid type III implementation-effectiveness design.

This pilot intervention will utilize an evidence-based process (i.e., implementation mapping) [38] and test primary implementation outcomes of penetration and cost, [48, 49] and secondary impact on student health outcomes (i.e., weight status, food security, dietary behaviors).

